## Introduction

The surveillance of mother and fetus is crucial for detecting early warning signs of maternal and/or fetal distress in pregnancies with an increased risk for adverse maternal and/or fetal outcomes (1, 2). If worrying maternal and/or fetal signs during pregnancy are not recognized and treated appropriately, the risk of mortality and morbidity is increased for both (3, 4). The lack of appropriate treatment may potentially have lifelong health consequences for the mothers and infants who survive. Surveillance in high-risk pregnancies aims to optimize early diagnosis, treatment, and timing for delivery in order to optimize health outcomes (3, 4). Specialized obstetric surveillance, including cardiotocography (CTG; registration of the fetal heart rate pattern and uterine contractions), blood pressure, and urine and blood analyses, often requires antenatal hospitalization and/or frequent outpatient visits until delivery.

High-risk pregnancies that often require intensified surveillance include those with hypertension during the pregnancy (e.g., chronic hypertension, gestational hypertension, and preeclampsia) and those with preterm premature rupture of membranes [pPROM; preterm premature (prior to 37 weeks of pregnancy) rupture of fetal membranes prior to onset of labor], the latter conferring a risk of preterm birth and/or chorioamnionitis, with increased risk of maternal and/or fetal death. In addition, some women with a history of adverse obstetric outcomes have a propensity for recurrence (e.g., previous intrauterine fetal demise, fetal growth restriction, or severe preeclampsia), thereby requiring intensified surveillance in the following pregnancy to optimize maternal and offspring health outcomes.

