### Participant eligibility criteria

The patients eligible for participation in the study are ≥18 years old, Norwegian-speaking, singleton pregnant women requiring intensified follow-up after at least one initial comprehensive hospital assessment. The following indications for surveillance may be relevant for home monitoring (Table 1): hypertensive disorders (chronic hypertension, gestational hypertension, and/or preeclampsia), pPROM, and previous adverse obstetric outcomes (e.g., fetal death, severe preeclampsia, preterm delivery, and/or fetal growth restriction). Exclusion criteria for home monitoring include a clinical imminent health risk to the mother and/or fetus, including (but not restricted to) non-reassuring CTG, blood pressure, infectious or clinical signs or symptoms, and/or more than 1 h travel to the hospital. Women with an expected delivery or induction of delivery within a short period will not be recruited [e.g., preeclampsia at term (≥37 weeks), prelabor rupture of membranes (PROM) ≥37 weeks, or pPROM with indication for rapid delivery (e.g., discolored amniotic fluid, suspicion of chorioamnionitis or other severe infections, or pathological CTG)]. Insufficient support at home and a lack of understanding of the relevant HOME study's technical devices (to be tested before departure from the hospital) are also exclusion criteria for being offered home monitoring.

**Table 1 T1:** Clinical definitions of the inclusion criteria for home monitoring of high-risk pregnancies.

	Inclusion criteria	Additional definitions
1	Hypertensive disorders of pregnancy	
-	✓ Chronic hypertension	✓ Hypertension (systolic blood pressure ≥140 mmHg and/or diastolic blood pressure ≥90 mmHg) identified before or during the first 20 weeks of the present pregnancy
	✓ Gestational hypertension	✓ New-onset hypertension (defined above) at ≥20 gestational weeks during the present pregnancy
	✓ Preeclampsia	✓ Gestational hypertension (defined above) in addition to new-onset proteinuria or at least one other maternal sign of organ dysfunction according to International Society for the Study of Hypertension in Pregnancy criteria from 2018 (4)
2	Preterm premature rupture of membranes	✓ Rupture of membranes at <37 gestational weeks ✓ No present uterine contractions ✓ Cephalic presentation

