### Outcome measures

The primary outcome variable is a composite of severe adverse events, as detailed in Table 2. These include maternal mortality, severe maternal morbidity/organ damage [e.g., sepsis, eclampsia, cerebral hemorrhage, acute respiratory distress syndrome, liver rupture, pulmonary embolism, amniotic fluid embolism, hemolysis, elevated liver enzymes, and low platelets (HELLP), HELLP without hemolysis (ELLP), and/or disseminated intravascular coagulation (DIC)], and fetal or early neonatal death. The primary composite outcome will be thoroughly evaluated by the Diagnostic Advisory Group (DAG). The members of the DAG include three senior obstetricians, one senior pediatrician, and one experienced midwife, all of whom are employed at Oslo University Hospital but are unrelated to and independent of the study group members and principal investigator (PI). All separate primary outcome events will be presented to the DAG, who will discuss and evaluate whether the events are related to the study or not, and whether the events could have been prevented or not.

**Table 2 T2:** Description of the clinical outcome variables of the HOME study.

Variable category	Variable	Definition/description	Evaluated by the Diagnostic Advisory Group
Primary composite outcome	Maternal death (direct)	Maternal death during pregnancy until 42 days postpartum due to pregnancy complications	Yes
	Severe maternal morbidity/organ damage	• Sepsis • Eclampsia • Cerebral hemorrhage • Acute respiratory distress syndrome • Liver rupture • Pulmonary embolism • Amniotic fluid embolism • HELLP (hemolysis, elevated liver enzymes, low platelets)/ELLP (HELLP without hemolysis) • DIC (disseminated intravascular coagulation)	
	Fetal/neonatal death	Intrauterine fetal death or death first 4 weeks after birth	
Secondary maternal outcomes Secondary offspring outcomes	Chorioamnionitis	Clinical diagnosis	No
	Malignant hypertension	Persistent systolic blood pressure ≥160 mmHg and/or diastolic blood pressure ≥100 mmHg	
	Adverse neonatal outcome	*Apgar* score <7 at 5 min of age *Umbilical cord acidemia* (arterial pH ≤7.10) *Metabolic acidosis* (umbilical artery pH <7.00 combined with base deficit in the extracellular fluid ≥12 mmol/L) (18)	
	Neonatal intensive care unit	Days	
	Respirator/ventilation support treatment	Days	

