The secondary study outcomes (Table 2) include maternal morbidity [chorioamnionitis and malignant hypertension (persistent systolic blood pressure ≥160 mm Hg and/or diastolic blood pressure ≥100 mmHg)] and adverse neonatal outcomes (Apgar score <7 at 5 min, cord acidemia, metabolic acidosis (18), admission to neonatal intensive care unit, and/or respirator/ventilation support treatment). Umbilical cord acid-base data will be validated according to the method described by Kro et al. (19, 20).

In addition to the daily reports, the patient-reported outcome measures in the HOME study will be collected by digital questionnaires sent to the study participants' smartphones 2–7 days after hospital admission or start of home monitoring, and again at 10–12 weeks postpartum, for study group comparison. One digital reminder will automatically be sent to non-responders. The validated questionnaires include the Bergen Insomnia Scale (21), the General Perceived Self-Efficacy Scale (22), Sense of Coherence-13 (23), Edinburgh Postnatal Depression Scale (24–26), and the 25-item version of the Hopkins Symptom Checklist (27, 28). In addition, explanatory variables for multivariable analyses will be added, including a history of depression (based on DSM-IV criteria) (26, 29) and major life events during the previous 12 months, including serious events related to marriage, family, friends, work, or health (26), selected from established life event scales (26, 30, 31). In addition, a few HOME study-specific questions/items were constructed for the particular study that are not validated. After completing the questionnaires, the participants will be informed about available help resources if they are in need of further mental support during a potentially demanding period in their life (e.g., from their primary healthcare provider or a Norwegian mental health organization that is available 24/7).

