### Data analysis

After inclusion in the study, baseline data such as patient demographics, medical and obstetric history, and pregnancy data will be collected and registered in a case report form before entering and coding the data in a study-specific electronic record. After delivery, the remaining relevant data for the assessment of maternal mortality and morbidity and perinatal outcomes will be collected from the hospital's electronic patient journal and registered in the study-specific HOME records. All primary and secondary outcome data will be registered, in addition to gestational age at birth and birthweight (Table 2).

The composite primary outcome will be analyzed using logistic regression analyses. Parity and gestational age will be included as potential confounding variables. Further, each component of the composite primary outcome and all secondary outcomes will be analyzed to provide further insight into the research question. The results will be presented as odds ratios with 95% confidence intervals, in addition to crude proportions (not adjusting for parity and gestational age).

The obstetric experts in the DAG will independently evaluate all composite primary outcomes continuously throughout the project period and without interference from anyone in the project group. The DAG will conclude whether any primary (severe adverse) outcomes are related to the study or not, and the results will be presented in detail in the study report.

The study participants' experience, mental wellbeing (depression and anxiety), sense of coherence, and self-efficacy will be described at the group level (hospital monitoring vs. home monitoring) at the two investigated time points (2–7 days after hospital admission or start of home monitoring and again at 10–12 weeks postpartum).

The cost-effectiveness of home monitoring compared to the hospital-monitored group will be described at the group level based on the estimated cost of each admission to different wards at Oslo University Hospital and outpatient visits from inclusion in the HOME study until delivery.

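### Chorioamnionitis and severe hypertension are to be compared without regard to inclusion indication, so an uneven indication mix can bias the comparison and pooling can dilute a true effect

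*Protocol article*

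**What the plan says.** All quotes are from the protocol article.

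- **Cohort.** Participant eligibility criteria pools three indications: hypertensive disorders, pPROM and previous adverse obstetric outcomes ("The following indications for surveillance may be relevant for home monitoring (Table 1").
- **Outcomes.** Outcome measures lists two secondary maternal outcomes: "maternal morbidity [chorioamnionitis and malignant hypertension". Table 2 defines the first as a clinical diagnosis and the second as "Persistent systolic blood pressure ≥160 mmHg and/or diastolic blood pressure ≥100 mmHg". Neither definition is tied to an indication.
- **Link to indication.** The Introduction describes pPROM as "the latter conferring a risk of preterm birth and/or chorioamnionitis". Under Home-monitored group details, temperature and CRP are recorded for pPROM women, and blood pressure and urine protein for hypertensive women.
- **Analysis.** Data analysis states that "Parity and gestational age will be included as potential confounding variables", and then that "each component of the composite primary outcome and all secondary outcomes will be analyzed to provide further insight into the research question". Results are odds ratios with 95% confidence intervals, "in addition to crude proportions (not adjusting for parity and gestational age". The covariate sentence follows the one on the primary outcome, but that last parenthesis implies the same two covariates throughout. Indication is not mentioned.
- **Allocation.** Women were not randomized. The hospital group was recruited mostly before home monitoring began in June 2024, and allocation follows equipment availability.

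**The concern.** Each of these two outcomes has a baseline risk that should differ sharply by indication. Two consequences follow if the analysis is carried out as written.

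1. **Confounding by indication mix.** Nothing in the design holds the share of pPROM or hypertensive women equal across groups recruited largely in different periods. If the home group has fewer pPROM women, its crude chorioamnionitis proportion is lower even when monitoring has no effect. If it has more, the bias runs against home monitoring. Adjusting for parity and gestational age does not directly correct this.
2. **Dilution.** If home monitoring raises chorioamnionitis among pPROM women only, averaging over women with little risk shrinks the difference. This happens even when the groups have the same mix.

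At stake is a safety signal. Infection is an obvious harm to look for when pPROM women are followed at home, and a pooled figure could reassure falsely or alarm falsely.

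**Working it through.** **The plan's own figure.** The only calculated figure is the primary sample size. With 10% in both groups, a 10-point margin, one-sided 5% and power 0.80: n = 2 × 0.10 × 0.90 × (1.645 + 0.842)² / 0.10² = 111.3, so 112 per group and 224 in total. Adding 6 and 20 gives 250, or 125 per group. This reproduces. It does not bear on the point except that 125 per group is used below.

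**Assumed inputs.** The article gives neither the indication split nor risks by indication. Set A: chorioamnionitis 20% in pPROM and 1% in other women, with a hospital pPROM share of 40%. Set B: 25% in the at-risk indication and 2% in others.

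**Formula.** Group proportion = share × risk in the at-risk indication + (1 − share) × risk in the others. The odds ratios are crude, home versus hospital.

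**Mix alone, no true effect, set A**
- Hospital: 0.40 × 0.20 + 0.60 × 0.01 = 0.0860.
- Home, 25% share: 0.25 × 0.20 + 0.75 × 0.01 = 0.0575.
- Odds ratio: (0.0575/0.9425) / (0.0860/0.9140) = 0.65.
- Home share 40%: odds ratio 1.00. Home share 50%: 0.50 × 0.20 + 0.50 × 0.01 = 0.105, odds ratio 1.25.

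**Mix alone, no true effect, set B**

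| Share home / hospital | Difference (points) | Odds ratio |
|---|---|---|
| 33% / 33% | 0 | 1.00 |
| 30% / 35% | −1.1 | 0.87 |
| 25% / 35% | −2.3 | 0.75 |
| 25% / 45% | −4.6 | 0.60 |
| 20% / 50% | −6.9 | 0.45 |

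The standard error of the difference is about 3.6 to 3.8 points. The bias is thus below one standard error at a 10-point imbalance and above it at 20 points. If the outcome is less specific to one indication (30% versus 10%), 20% / 50% gives 0.65 rather than 0.45.

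**How large an imbalance could arise by chance?** With an expected share of one third in both groups, the standard error of the difference in shares is √(2 × 1/3 × 2/3 / 125) = 6.0 points, so ±11.7 points at 95%. A 10-point imbalance needs no systematic cause.

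**True odds ratio of 2 within pPROM, set A.** The odds rise from 0.25 to 0.50, so the risk goes from 20% to 33.3%. The pooled odds ratio for a home share of 20%, 25%, 30% and 40% is 0.86, 1.06, 1.27 and 1.72.

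**Dilution with equal shares.** With 33% at risk in both groups, a rise from 20% to 30% in those women, and 2% in the others: hospital 0.33 × 0.20 + 0.67 × 0.02 = 0.0794; home 0.33 × 0.30 + 0.67 × 0.02 = 0.1124. The difference is 3.3 points instead of 10, and the odds ratio 1.47 instead of 1.71.

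**The case against.** The strongest case against has five parts.

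- **Silence on the denominator.** A reader might infer that the article fixes all women as the denominator. It does not say so, and an analysis plan that is not shown could set one. That stands. But the article does go into covariates and presentation, and what it names there omits indication.
- **No evidence of imbalance.** A reader might also infer that the group difference will mainly reflect the indication mix. The documents do not support this. They give no split, say that allocation follows equipment availability, and leave the direction open. The bias is nil under balance and within sampling error for moderate imbalance: in set A at 40% versus 25%, it is 2.9 points against a standard error of 3.3. What remains is that nothing prevents an imbalance.
- **Neither outcome belongs to one indication.** This stands. The Introduction says that pPROM raises the risk of chorioamnionitis, not that other women are free of it. Previous severe preeclampsia is an inclusion reason, and the Introduction describes such histories as prone to recur. Limiting the hypertension outcome to women included for hypertension would leave out women at risk. An all-women comparison is a legitimate target for a study of selected high-risk pregnancies.
- **Restriction costs precision.** This stands. In set A, about 50 and 31 pPROM women would be compared. With no effect, the 95% interval for the odds ratio is about 0.33 to 3.06, and power at a true odds ratio of 2 is about 27%. Pooling is no remedy, because it estimates a different and smaller quantity.
- **Secondary outcomes only.** This stands and limits the weight of the point.

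**Conclusion.** The point holds as a risk of confounding and dilution for two secondary outcomes. It does not show that the comparison is already biased. As described, the analysis neither separates nor adjusts for inclusion indication, although the groups are non-randomized and largely sequential and both outcomes depend strongly on indication.

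Under the assumed risks, mix alone moves the crude odds ratio from 1.00 (equal shares) to about 0.75 at a 10-point and 0.60 at a 20-point lower share at home, and above 1 if the home share is higher. A true doubling of the odds within pPROM can appear as anything from 0.86 to 1.72, depending on the home share (20% to 40%, against 40% in hospital). These figures are for crude comparisons. Adjustment for gestational age might remove part of the bias if it tracks indication, but the article gives no basis for counting on that. The conclusion on the primary composite is not affected by this point.

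**What to change.** In Data analysis, with a matching note to Table 2, for chorioamnionitis and the severe-hypertension outcome:

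1. Show numerators and denominators per group by the indication recorded at inclusion, with a stated rule for women who meet more than one.
2. Name chorioamnionitis among women included for pPROM as a specific comparison.
3. Keep the all-women comparison for both outcomes, but adjust it for, or stratify it by, indication in addition to parity and gestational age.
4. Do not restrict the severe-hypertension outcome to women included for hypertension, because women included for previous severe preeclampsia are also at risk.

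Item 2 is needed as well as item 3: adjustment removes the mix bias, but a single adjusted odds ratio still assumes one common effect across indications.

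**Cost.** A few sentences and no new data, since baseline pregnancy data are already collected at inclusion. Intervals within indication will be wide. Events are few: in set A about 11 (125 × 0.086) plus 7 (125 × 0.0575), or 18 in all. A stratified estimate may therefore be steadier than a regression with several added terms, and the within-indication results should be read as descriptive.

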### Sample size

The sample size calculation is based on the non-inferiority design and will be calculated for the primary clinical composite outcome (described above and in Table 2). The non-inferiority margin was set to 10% (i.e., a difference larger than 10% will be considered clinically significant), based on careful clinical considerations. The expected proportion of the outcome was set to 10%, based on the rate of the primary composite outcome observed in the first 80 women recruited to the hospital-monitored group in the HOME study. If there is no true difference between the home-monitored and the hospital-monitored groups' primary composite outcomes (10% in both groups), a total of 224 women with high-risk pregnancies (112 women in each group) is required. With this number of participants, we have a power of 0.80, ensuring that the upper limit of a one-sided 95% confidence interval will exclude a difference in favor of the hospital-monitored group of more than 10%. An additional six women will be invited to take potential dropouts into account. Further, due to the non-parallel group design (women were not randomized to either group, but are first mainly allocated to the hospital-monitored group and then to the home monitored group, pending on availability of home monitoring resources and equipment), another 20 women will be recruited to adjust for potential confounding factors such as parity and gestational age (totalling 250; 125 women in each group).

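### The non-inferiority margin is a 10-point risk difference, but the confounder-adjusted primary result is planned only as an odds ratio, so it cannot be judged against the margin

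*Protocol article*

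**What the plan says.** **Protocol article, Sample size.** The margin is given as a difference: "The non-inferiority margin was set to 10% (i.e., a difference larger than 10% will be considered clinically significant"). The anticipated risk is the same in both groups: "The expected proportion of the outcome was set to 10" per cent, taken from the first 80 hospital-monitored women. The required number follows: "10% in both groups), a total of 224 women with high-risk pregnancies (112 women in each group) is required". The success criterion behind the power of 0.80 is that "the upper limit of a one-sided 95% confidence interval will exclude a difference in favor of the hospital-monitored group of more than 10" per cent. Six women are added for dropout. Because the groups are not randomised and the hospital group is filled mainly before the home group, 20 more are added to allow for confounding ("totalling 250; 125 women in each group").

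**Protocol article, Data analysis.** "The composite primary outcome will be analyzed using logistic regression analyses", with parity and gestational age as potential confounders. After a sentence on the components of the composite and the secondary outcomes, the reporting scale is fixed: "The results will be presented as odds ratios with 95% confidence intervals, in addition to crude proportions (not adjusting for parity and gestational age"). It is not said whether these intervals are one-sided or two-sided. No interval is named for the difference in crude proportions, no odds-ratio margin is given, and nothing links the adjusted result to the 10-point margin.

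**Protocol article, Discussion.** Non-inferiority on severe maternal and fetal outcomes remains the aim.

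**The concern.** The sample size section and the analysis section describe results on two different scales. The first needs a risk difference with a one-sided limit. The second produces an adjusted odds ratio with an interval, plus crude proportions. The adjusted estimate is the one that the authors themselves consider necessary, since they enlarge the study to pay for it, yet it is the one that cannot be held against the margin. The estimate that can be held against it leaves out the adjustment, although the hospital group was recruited from December 2022 and the home group only from June 2024.

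At stake is the main safety conclusion, on a composite that includes maternal, fetal and neonatal death. If the analysis section is followed literally, the team must choose after seeing the data between a crude comparison with the margin and an improvised rule for the odds ratio. These choices can give different answers.

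**Working it through.** **Inputs.** From Sample size: risk 0.10 in both groups, margin 0.10, one-sided 5%, power 0.80, 112 per group required and 125 per group planned. From Data analysis: adjusted odds ratio with 95% interval, and crude proportions.

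**1. Reproduce the stated number on the risk-difference scale.**

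n per group = 2 × 0.10 × 0.90 × (1.645 + 0.842)² / 0.10² = 111.3, so 112. This matches.

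Power check: SE = √(0.18/n).
- n = 112: SE = 0.0401; 0.10/SE = 2.494; Φ(2.494 − 1.645) = 0.802.
- n = 125: SE = 0.0379; 0.10/SE = 2.635; Φ(2.635 − 1.645) = 0.839.

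The margin is therefore an absolute difference of 10 points, judged at one-sided 5%.

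**2. Can the planned odds ratio be compared with that margin?** The odds ratio equivalent to a 10-point excess depends on the hospital-group risk p: OR = [(p + 0.10)/(0.90 − p)] / [p/(1 − p)].

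| Hospital-group risk | OR equal to +10 points |
|---|---|
| 5% | 3.35 |
| 10% | 2.25 |
| 15% | 1.89 |
| 20% | 1.71 |

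The article fixes no reference risk for such a conversion, and its 10% comes from 80 women.

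**3. What the planned outputs offer.**

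| Output | Adjusted? | On the margin's scale? |
|---|---|---|
| Logistic regression odds ratio, 95% interval | Yes | No |
| Crude proportions | No | Yes, once a difference and its limit are derived |

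No row has yes in both columns.

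**4. How far improvised rules could depart from the design.** The article proposes none of these rules; each is an assumption for illustration, and all figures are unadjusted.

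(a) *Two-sided 95% interval on the risk difference, against 10 points.* Power = Φ(0.10/SE − 1.960): Φ(0.534) = 0.703 at 112 and Φ(0.675) = 0.750 at 125. For 80%, n = 0.18 × (1.960 + 0.842)²/0.01 = 141.3, so 142 per group.

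(b) *Odds ratio against an assumed margin of 2.25, one-sided 95% limit.* SE(log OR) = √(2/(0.09n)) = 0.445 at 112 and 0.422 at 125; ln 2.25 = 0.811. Power = Φ(1.821 − 1.645) = 0.570 and Φ(1.923 − 1.645) = 0.610. Exact enumeration gives 0.566 and 0.598. At 125 per group with 10% risk in both, this rule and the risk-difference rule (both one-sided 5%) disagree in about 25% of trials.

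(c) *An odds-ratio interval that includes 1 is read as non-inferior.* Take true risks of 20% (home) and 10% (hospital). SE(log OR) = √(1/(0.16n) + 1/(0.09n)) = 0.394 at 112 and 0.373 at 125. The chance of passing is Φ(1.960 − 2.060) = 0.46 and Φ(1.960 − 2.176) = 0.41. Exact enumeration gives 0.45 and 0.40. The design rule passes this case about 5% of the time.

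**The case against.** The strongest reply is that the article does contain a decision criterion. Sample size states scale, margin, direction and confidence bound, and the sentence in Data analysis concerns presentation across all clinical outcomes. It does not say that the odds ratio replaces the criterion. A logistic model can also yield a standardised risk difference, and the method for its interval is a detail that a condensed article may leave to an analysis plan.

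Much of this stands, and it rules out three stronger readings that a reader might infer.

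- *That the study has no decision rule.* It has one. What is missing is a statement that it applies to the adjusted estimate.
- *That the analysis yields nothing but an odds ratio.* Crude proportions are also planned, and a crude risk difference with a one-sided limit could be computed from them.
- *That the 80% power is lost.* Under the stated criterion, unadjusted power is 80% at 112 and 84% at 125 per group. It falls only if another rule is substituted. A conflict of confidence level cannot be asserted either, because the sidedness of the 95% intervals is not given and a two-sided interval for reporting can coexist with a one-sided test.

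The reply does not remove the mismatch. The article is not silent on the effect measure: it names the odds ratio for the adjusted analysis and marks the absolute-scale output as unadjusted. An analysis plan that followed it faithfully would inherit the problem.

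**Conclusion.** The concern holds as a mismatch between two stated rules. The margin is an absolute difference of 10 points, confirmed by exact reproduction of 112 per group, while the only adjusted result planned is an odds ratio. An odds ratio cannot be compared with that margin without a reference risk, since the equivalent value runs from 3.35 to 1.71 as the hospital-group risk goes from 5% to 20%. The one comparable result is unadjusted in a non-randomised comparison recruited largely in sequence.

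The consequences in step 4 of the working depend on the assumed rules named there: power of 70% to 75% with a two-sided 95% interval on the difference, 57% to 61% with an assumed odds-ratio margin of 2.25 and a one-sided limit, and a 40% to 46% chance of passing a true 20% versus 10% if an interval including 1 were accepted. They show why the rule should be fixed beforehand; they are not predictions of what the plan as written will do. The power of an adjusted risk difference was not calculated, as it depends on how parity and gestational age differ between the groups.

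This should be corrected before the primary analysis, because it decides how the main safety conclusion is reached.

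**What to change.** Keep the logistic model with parity and gestational age. Define the primary estimate as the adjusted risk difference, home minus hospital, by marginal standardisation: predict each woman's risk under both forms of monitoring, average over the study population, and subtract. Give it a delta-method or bootstrap interval.

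State the rule in Data analysis: non-inferiority is declared only if the upper one-sided 95% limit of this difference, which is the upper bound of the two-sided 90% interval, is below 10 percentage points. Report the odds ratio with its 95% interval as supportive, say whether that interval is two-sided, and add that an odds-ratio interval including 1 is not evidence of non-inferiority. Crude proportions can stay as description.

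The cost is a short change of wording and a few lines of code. It needs no new data and no additional women, and leaves the margin and the planned 250 unchanged.

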The cost of home monitoring will be compared to hospital monitoring, including the maternal costs until delivery, but excluding maternal and newborn healthcare costs after delivery. The health economics assessment will evaluate hospital costs, including costs related to health professionals and administrative personnel time, for both outpatient and inpatient care. The mean cost per outpatient consultation and inpatient hospital cost per day will be calculated. The estimated mean cost is multiplied by the number of registered contacts at different departments during the study time (until delivery). Using the overhead indirect cost method, we will calculate the average estimated mean cost for different wards where the patient has a registered contact at the Oslo University Hospital. All costs will be evaluated as if operating under steady-state conditions based on the budget of 2023. Prices will be converted from Norwegian crowns (NOK) to U.S. dollars (US$) using the mean exchange rate for 2023 of 1 US$ = 9.86 NOK. All patient costs will be covered by the Norwegian public insurance system.

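### The only cost analysis stated is a group-level description of costs from inclusion to delivery, so a group difference in gestational age at inclusion or in indication would appear as a cost difference.

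*Protocol article*

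**What the plan says.** Under Outcome measures, the protocol article sets a between-group aim: "The cost of home monitoring will be compared to hospital monitoring, including the maternal costs until delivery". Each woman's cost is built from mean unit costs (per outpatient consultation, per inpatient day, by ward) multiplied by her number of registered contacts up to delivery. Prices are standardised to the 2023 budget.

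Under Data analysis, the method is one sentence. It begins "The cost-effectiveness of home monitoring compared to the hospital-monitored group will be described at the group level", and the costs it covers are those of admissions and "outpatient visits from inclusion in the HOME study until delivery". No covariate, matching or interval is stated for cost.

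Under Sample size, the article says "women were not randomized to either group, but are first mainly allocated to the hospital-monitored group and then to the home monitored group", depending on equipment. It adds that "another 20 women will be recruited to adjust for potential confounding factors such as parity and gestational age".

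Under Data analysis, adjustment for parity and gestational age is stated directly after the logistic regression of the primary composite. Results of that paragraph are to be odds ratios and crude proportions.

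**The concern.** A total that starts to accumulate at inclusion depends on when inclusion happens. A woman included at an earlier gestational age has, other things equal, a longer window to delivery and more contacts, whichever way she is monitored. Indication acts in the same way, since it affects both when a woman enters and how intensively she is followed.

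The eligibility criteria admit chronic hypertension, gestational hypertension, preeclampsia, preterm rupture of membranes before 37 weeks, and previous adverse outcomes. These can bring women in at very different points in pregnancy, and no entry window or matching on gestational age is stated. The hospital group was recruited mainly from 2022 to 2024 and the home group from June 2024, so the mix of indications could drift between the periods. Fixing prices to one budget year removes price drift but does nothing about time at risk of cost.

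The result is meant to be used. The abstract and Introduction expect lower costs with home monitoring, and the Discussion includes economic costs in what the non-inferiority comparison will address. A crude description could then be read as a saving or an excess due to home monitoring when part or all of it reflects when and why women entered.

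**Working it through.** **The plan's own figures.** The article gives no numerical target for cost, so there is none to reproduce. The sample size does reproduce. With 10% expected in both groups, a 10-point margin, one-sided 5% and power 0.80:

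n per group = (1.645 + 0.842)² × (0.10 × 0.90 + 0.10 × 0.90) / 0.10² = 6.185 × 0.18 / 0.01 = 111.3, rounded up to 112.

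The total is 224, and 224 + 6 + 20 = 250. The point does not depend on this figure. It matters only that the last 20 women are there because the plan expects to adjust for gestational age and parity.

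**The statements side by side.**
- Cost window: inclusion to delivery, so its length varies by woman (Data analysis).
- Cost construction: unit cost × contacts, so it grows with time in the study (Outcome measures).
- Allocation: not randomised, mainly sequential (Sample size).
- Confounders named by the plan: parity and gestational age (Sample size).
- Adjustment stated for the primary outcome: yes. For cost: none stated (Data analysis).

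**Illustration by arithmetic.** Assume equal and constant weekly cost in both groups, the same timing of delivery, and therefore no true cost effect. Let W be the mean hospital-group window in weeks and d the number of weeks by which the home group is included earlier. The crude cost ratio is (W + d) / W. Neither W nor d is in the documents; both are assumed.

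| W (weeks) | d = 0.5 | d = 1 | d = 2 |
|---|---|---|---|
| 3 | 3.5/3 = 1.167 | 4/3 = 1.333 | 5/3 = 1.667 |
| 5 | 5.5/5 = 1.10 | 6/5 = 1.20 | 7/5 = 1.40 |
| 8 | 8.5/8 = 1.062 | 9/8 = 1.125 | 10/8 = 1.25 |

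If the home group is included later instead, the sign reverses. For d = 1 the ratios are 2/3 = 0.667, 4/5 = 0.80 and 7/8 = 0.875.

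**Illustration by simulation.** 125 women per group, 2,000 runs. Inclusion is near 31 weeks in the hospital group (SD 3) and delivery near 37 weeks (SD 1.5). Weekly cost varies between women but has the same mean in both groups, so again there is no true effect. The difference in mean cost is given as a share of the hospital mean:

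| Home group included earlier by | Crude | Adjusted for gestational age at inclusion |
|---|---|---|
| 0 weeks | 0.8% | 0.6% |
| 0.5 weeks | 8.4% | 0.6% |
| 1 week | 16.5% | 0.4% |
| 2 weeks | 32.3% | 0.3% |

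The simulation shares the constant-mean-cost assumption with the arithmetic. It shows the mechanism and that the covariate removes the shift. It is not evidence of how large the shift will be in this study.

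**The case against.** The strongest reply is that the article never says costs will go unadjusted. The same group-level phrase is used there for the patient-reported outcomes, yet Outcome measures mentions explanatory variables for multivariable analyses in that context. So the phrase does not by itself exclude modelling. The abstract also lists cost among the secondary outcomes, and Data analysis says all of those will be analysed. A link function and an interval method are what an article commonly leaves to a fuller plan.

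Part of this stands. A reader might infer that the plan rules out adjustment for cost; the text does not support that, and the absence is inferred. But no statement about multivariable analysis is made for cost, Table 2 lists no cost outcome, and the odds ratios and proportions of the regression paragraph cannot serve a cost total. A descriptive method is the only one stated for a comparison the authors intend to interpret. The issue is that method set against the plan's own named confounders, not missing modelling detail.

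A reader might also infer that the groups do differ, or take a particular percentage as the expected bias. The documents support neither. They give no gestational age at inclusion and no duration of monitoring. Both groups must meet the same inclusion criteria, and some hospital-monitored women are recruited concurrently from 2024. Cost need not accrue at a constant rate either, since unit costs differ by ward and visits are set individually.

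**Conclusion.** The point holds in conditional form. Followed as written, the cost comparison is a crude contrast between non-randomised, mainly sequential groups, over a window whose start can differ systematically between them. Any difference in gestational age at inclusion or in indication would be counted as a cost difference. Size and direction are unknown. The range of about 33% down to 12.5% for a one-week imbalance is illustrative only and rests on an assumed mean window of 3 to 8 weeks, equal and constant weekly cost, and the same timing of delivery. The change should be made, in proportion to a secondary outcome.

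**What to change.** Keep the crude group means as description. Add, as the main cost comparison, the adjusted difference in mean cost per woman with its confidence interval, for example from a linear regression with bootstrap intervals or a gamma generalised linear model. The choice between them is secondary. Adjust for gestational age at inclusion, parity and indication.

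State explicitly that the covariate is gestational age at inclusion. Gestational age at birth and time in the study can both be affected by the monitoring and should not be adjusted for. For the same reason, do not rely on cost per monitored day: its denominator is a duration that monitoring may change.

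The cost is a little extra analysis work and one check. Data analysis describes the baseline data only in general terms, and the gestational age it names as registered is that at birth. The sponsor should confirm that gestational age at inclusion is recorded.
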